### Measurements (measurement times)

#### Baseline evaluation basal (T0)

▪ The data obtained in the examination made prior to beginning treatment will include personal and sociodemographic characteristics, background and case history, ankle/arm index, nutritional status, previous treatment received, results of the ulcer exudate culture, the dimensions of the ulcer and observations regarding its condition, location and duration in an active state, as well as about the patient's health-related quality of life.

▪ Follow up. At each visit, the nurse applying the treatment will record the macroscopic status of the ulcer, any adverse events that may have occurred, the time employed in providing the treatment, the location of the treatment (clinic/home) and the name of the person performing it. If total healing of the ulcer is detected during a routine examination, the treatment programme official at the relevant Clinic should be informed. For the patients in Group A, a record should also be kept of the data concerning the acupuncture session (the number and location of local points).

#### Follow-up evaluation at 3 months after starting treatment (T1)

At three months after starting the treatment, a fresh assessment will be made of the patient's condition, quality of life and compliance with hygiene-posture recommendations, as well as of the physical status of the ulcer (appearance and size).

#### Follow-up evaluation at 6 months after starting treatment (T2)

With the same content as the previous evaluation.

#### Follow-up evaluation at 12 months after starting treatment (T3)

With the same content as the previous evaluation.

### Data analysis

The data analysis will be carried out by personnel blinded to the treatment groups, and for two types of populations: (1) intention to treat (ITT), with all the patients randomized; (2) per protocol (PP), including only the patients with no more than slight variances from the protocol.

The baseline variables for the different groups will be compared, to test the homogeneity produced by random allocation, in terms of differences of the means and of proportions, and the only differences taken into consideration in this comparison will be those that are clinically relevant for subsequent analysis. The magnitude of the difference in any imbalance produced by the random allocation to groups will be evaluated by using ratios of the means, or medians, or proportions, bearing in mind whether the level of analysis is per cluster or per individual.

The final analysis will be carried out as a univariate survival analysis (using the Kaplan-Meyer method and the log-rank-test for inter-group comparison). The hazard ratios for each treatment will be calculated, together with the corresponding NNTs, calculating a 95% confidence interval, using Cox's proportional risk regression model. The assumption of proportionality will be assessed from the interaction between the time elapsed until success (total healing) and treatment group, and will be tested graphically by observing the parallelism in the log-log curves. A multilevel analysis will be carried out to adjust for possible unbalanced variables in the baseline analysis, taking the patients as level 1 and the Primary Healthcare Clinics as level 2. The interactions between clinic and treatment group will be examined, as will the possible variability in the intercept. The level of significance will be set at p < 0.05, for all the tests made. Cost-effectiveness, cost-utility and opportunity cost analyses will be made.

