### Design

Open-labeled, controlled multicentre prospective study, with random cluster allocation to treatment groups (Primary Healthcare Clinics) in the Sevilla-Sur Health District (Andalusian Public Health System).

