#### Analysis units

per Healthcare Clinic (according to the group assigned) and per patient.

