### Sample size

The sample size has been calculated following the parameters of Campbell et al. [41], on the basis of historical data [18]. The success rate for complete healing of venous leg ulcers at 3 months, with compression bandaging plus special dressings, is 44%. With an alpha (significance) level of 0.05 and a power of detection of differences of 80%, assuming a two-tailed approach, the total sample size needed will be 375 patients, in order to detect differences of 15% between the groups, as regards the rate of complete healing of venous leg ulcers at 3 months. This calculation assumes a possible dropout rate of 5% and an intra-cluster coefficient of correlation of 0.05 (according to the expected variance of the response within a single cluster). There will be 15 clusters (Primary Healthcare Clinics) and so each Clinic will need to recruit 25 subjects. Therefore, 3 treatment arms will be formed, with 125 patients in each (with 5 Clinics per arm).

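### The named final test, a univariate log-rank, ignores that clinics were randomised; at the plan's own ICC its false-positive rate is about 18–29%, not 5%

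*Protocol article*

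**What the plan says.** The Design section describes a study "with random cluster allocation to treatment groups (Primary Healthcare Clinics"), and the Sample size section puts five clinics of 25 patients in each of three arms. That section allows for correlated outcomes within a clinic: it assumes "an intra-cluster coefficient of correlation of 0.05". The Analysis units entry reads "per Healthcare Clinic (according to the group assigned) and per patient".

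The primary outcome is time to complete healing. For its analysis the Data analysis section says: "The final analysis will be carried out as a univariate survival analysis (using the Kaplan-Meyer method and the log-rank-test for inter-group comparison"). It adds hazard ratios and NNTs with 95% confidence intervals from a Cox model, and applies a 0.05 significance level to every test. Neither the log-rank test nor the Cox model is given a clinic term, a frailty or a cluster-robust variance.

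The same section does plan a model with patients at level 1 and clinics at level 2, and gives its purpose: "A multilevel analysis will be carried out to adjust for possible unbalanced variables in the baseline analysis". It will also look at variability in the intercept and at clinic-by-treatment interaction.

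**The concern.** Patients in one clinic share nurses, habits and case mix, so their healing times are correlated. When whole clinics are allocated, that correlation adds directly to the variance of the treatment comparison. A log-rank test that takes patients as independent leaves this variance out, so its p-values are too small. Confidence intervals from a Cox model without a clinic term are too narrow for the same reason.

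The protocol recognises the correlation when it sets the sample size and drops it in the analysis it calls final. Adjusting for unbalanced baseline variables does not address this, because within-clinic correlation inflates the variance even when every baseline variable is balanced. At stake is whether a significant result reflects the treatment or merely which five clinics happened to receive it.

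**Working it through.** **Inputs.** From Sample size: two-sided alpha 0.05, ICC 0.05, 25 patients per clinic, five clinics per arm, 5% dropout, 44% healed at 3 months. From Interventions: one year of follow-up. From Data analysis: ordinary log-rank test at 0.05. The protocol states no design effect, so it is derived here.

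**1. Design effect.** DE = 1 + (m − 1) × ICC.
- m = 25: 1 + 24 × 0.05 = 2.20.
- m = 25 × 0.95 = 23.75 after dropout: 1 + 22.75 × 0.05 = 2.14.

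**2. True size of a pairwise test that ignores clustering.** Size = 2 × (1 − Φ(1.96/√DE)).
- DE 2.20: 1.96/1.483 = 1.321, giving 18.6%.
- DE 2.14: 1.96/1.462 = 1.341, giving 18.0%.

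**3. Interval width.** The unadjusted interval is 1/√2.2 = 0.67 of its proper width, so about 33% too narrow.

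**4. Three-arm log-rank (2 df).** Size = exp(−5.991/(2 × 2.2)) = 25.6%.

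**5. Simulation under the null.** 4,000 trials per setting, with 15 clinics of 25, exponential healing times, 5% dropout and the ordinary log-rank test. A log-normal clinic effect on the healing rate was calibrated to 44% healed and the stated ICC at 3 months (SD 0.353 on the log scale for ICC 0.05). Pairwise false-positive rates:

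| ICC | DE (m = 25) | Formula | Simulated, 3 months | Simulated, 12 months |
|---|---|---|---|---|
| 0 | 1.00 | 5.0% | 5.0% | 5.2% |
| 0.02 | 1.48 | 10.7% | 10.7% | 15.6% |
| 0.05 | 2.20 | 18.6% | 18.6% | 28.8% |
| 0.10 | 3.40 | 28.8% | 29.0% | 40.2% |

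The first row recovers the plan's nominal 5%, so clustering is the cause of the excess. Further simulations at ICC 0.05 gave 19–20% at 3 months and about 29% at 12 months. The three-arm test rejected in 26.0% (3 months) and 41.8% (12 months). A clinic-level t analysis on 12 df rejected in 5.0–5.4%.

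**6. Why 12 months is worse.** About 43% of patients have healed by 3 months and 86.5% by 12, so the variance that the log-rank test counts shrinks while the between-clinic part does not. On the log hazard ratio scale for two arms (250 patients):
- Between-clinic variance: 2 × 0.353²/5 = 0.050.
- Counted variance, 3 months: 4/(250 × 0.431) = 0.037. Inflation is 1 + 0.050/0.037 ≈ 2.3, and size about 20%.
- Counted variance, 12 months: 4/(250 × 0.865) = 0.0185. Inflation is 1 + 0.050/0.0185 ≈ 3.7, and size about 31%.

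This rough calculation agrees with the simulation.

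**7. Does the two-level model repair this?** Its stated purpose is baseline adjustment, its outcome is not specified, and another analysis is called final. The planned clinic-by-treatment interaction does not help either: each clinic delivers one treatment, so clinic is nested in arm and that interaction cannot be estimated.

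**The case against.** The strongest reply is that the plan does not overlook clustering. It uses an ICC, lists the clinic as an analysis unit, and commits without condition to a multilevel model with clinics at level 2 and attention to the intercept. Such a model would account for between-clinic variance in whatever outcome it is fitted to. On this view the defect is one of priority. That is a fair description, but priority decides the matter here: the unadjusted test is the one called final, and the clustered model is tied to a different purpose.

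Other points stand as qualifications:
- Independence is explicit for the univariate log-rank. For the Cox model it is inferred from the absence of any clinic term, and a condensed article could have left the variance estimator to an analysis plan.
- The method for few clusters could also sit in an analysis plan, so its absence alone is not an error.
- The size depends on the ICC, as the table shows. The 12-month figure further assumes that clinic differences stay constant for a year, which the documents do not say.
- At ICC 0.05, at least one of the three pairwise tests is falsely significant in roughly 38–54% of simulated trials. Part of that is multiplicity: without clustering the figure is already 12–13%. It should not be set against 5%.

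None of these makes the named test valid.

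**Conclusion.** The plan is wrong as written. Its deciding test of the primary outcome ignores the unit of randomisation, and the error is anti-conservative. At the protocol's own ICC of 0.05 and 25 patients per clinic, a nominal 5% pairwise comparison has a true size of about 18–20% by formula or at 3 months. A log-rank over the full 12 months has about 29%, if clinic effects persist. Even at an ICC of 0.02 the rate is 11–16%, at least double the nominal level. If the Cox model is fitted without a clinic term, the HR and NNT intervals share the fault.

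**What to change.** In the Data analysis section, name a clinic-adjusted comparison as the primary analysis of time to healing, to be done whether or not baseline is balanced. Either of these would serve:
- a Cox model with a clinic random effect (shared frailty), with a reference suited to few clusters: t on 15 − 3 = 12 degrees of freedom, or a permutation test over clinic allocations;
- a clinic-level analysis of log healing rates, with the same 12 degrees of freedom.

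Take the HR and NNT intervals from that analysis. Keep Kaplan-Meier curves as description and drop the unadjusted log-rank as the test. Baseline covariates can be added to the same model. Remove the clinic-by-treatment interaction, which this design cannot estimate.

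The change is to wording only and needs no new data, but intervals will widen and low power will become visible. With 125 per arm and a design effect of 2.2, the effective size is 125/2.2 ≈ 57 per arm, and power for 44% against 59% at 3 months is about 36%, or slightly less after dropout, before any penalty for few clusters. That shortfall belongs to the sample size and exists already; the unadjusted test only hides it.

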Developing a healthcare plan for VLU patients includes curing active ulcers and preventing relapses. To achieve these goals, such a plan must address the treatment of infections associated with these ulcers, preventing the development of infection, stimulating granulation and epithelial tissues, compression, raising the leg position, improving mobility, reducing obesity, improving nutrition and, in some cases, performing surgery [12,13].

Perhaps the most controversial aspect of the local treatment of VLUs concerns the type of dressings to use [14]. The use of wet dressings has been shown to favour granulation and epithelialization processes and, therefore, the healing of the ulcer, but no evidence has been provided to assist in choosing between special dressings and simple, low-adherence ones [15]. The application of external compression causes various complex physiological and biochemical effects that affect the venous, arterial and lymphatic systems. Provided the degree of compression does not adversely affect arterial blood flow, and that the correct techniques and materials are applied, the effects of compression may be very positive, reducing oedema and pain, whilst at the same time favouring the healing of ulcers caused by venous insufficiency. However, there are many ways in which this compression may be applied, and there is no consensus as to which is best [16]. Depending on the size of the ulcer, healing rates with compression treatment range from 40–70% at three months to 50–80% at 6 months [17,18]. The latest systematic review carried out by the Cochrane Collaboration recommends compression therapy and low-cost, low-adherence dressings as a first-line treatment for healing VLUs [15].

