### Outcome measures

#### Primary outcome

##### Time until complete healing is achieved

Complete healing is defined as the complete epithelialization of all the leg venous ulcers, not just the reference one.

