##### Changes in the size of the surface area of the ulcer (in cm^2^)

When the baseline evaluation is made, the ulcer will be measured; if there are more than one, the largest ("the main ulcer") will be assessed. Nevertheless, the outcome variable of complete healing will be determined on the basis of all the ulcers observed on the patient when the baseline assessment is made. The area of the ulcer will be calculated using a compact digital tablet (Visitrak), with which the area can be assessed quickly, conveniently and accurately. The outline of the ulcer is drawn on a tracing sheet used as the digital screen; this has three layers to minimize the risk of cross contamination or secondary infection, and the layer in contact with the patient is sterile. The surface on which the data are recorded is kept clean and may be included in the patient's case history.

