#### Covariables

The covariables recorded will be the patient's age, sex, educational level, occupation, income, weight (kg), height (cm), mobility, systolic arterial pressure, diastolic arterial pressure, arm/ankle index and ankle diameter (cm), the duration of the active ulcer (weeks), the location of the ulcer (if more than one ulcer is present, stating the location of the largest one, which is taken as the reference ulcer), whether the ulcer is unilateral or bilateral, the number of ulcers on the leg(s), whether the ulcer is new or recurrent (in the latter case, recording the time since the first appearance, in years and months), the signs of granulation at the base of the ulcer, the signs of epithelialization at the edges of the ulcer, the presence of fibrinous and/or necrotic tissue, the presence of lipodermatosclerosis, and the presence of infection. Other variables recorded will include dependence on tobacco, alcohol or other psychoactive substances, the presence of diabetes mellitus, the results of a nutritional study (haemogram and biochemical tests: albumin, prealbumin, transferrin and proteinogram), the time elapsed until recurrence occurs (weeks), compliance with hygiene-posture recommendations, self care, and the assistance or otherwise of non-professional carers. In addition, a record will be kept of all medication taken (corticoids, immunosuppressors, anticoagulants, etc.) and information about possible cultures of the ulcer exudate.

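### Covariate adjustment depends on baseline imbalance judged after the fact; naming baseline ulcer area in advance would gain precision at no cost

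*Protocol article*

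**What the plan says.** Four statements in the protocol article bear on this.

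- **Main analysis (Data analysis).** "The final analysis will be carried out as a univariate survival analysis", with Kaplan-Meier curves, a log-rank test and hazard ratios from a Cox model. The primary outcome is "Time until complete healing is achieved", counted over all of the patient's venous ulcers.
- **Choice of covariates (Data analysis).** "The baseline variables for the different groups will be compared, to test the homogeneity produced by random allocation". This comparison is then filtered: "the only differences taken into consideration in this comparison will be those that are clinically relevant for subsequent analysis". What passes the filter goes into a two-level model, with patients within clinics: "A multilevel analysis will be carried out to adjust for possible unbalanced variables in the baseline analysis". No covariate is fixed in advance, and nothing says how large a difference must be to count.
- **Prognosis (Background).** "Depending on the size of the ulcer, healing rates with compression treatment range from" 40–70% at three months to 50–80% at six months.
- **Data available (Outcome measures and Covariables).** "When the baseline evaluation is made, the ulcer will be measured"; where there are several ulcers, the largest is taken. Table 1 schedules both the area and the duration of the main ulcer at T0, and the Covariables section lists duration in weeks.

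**The concern.** The value of a baseline covariate lies mainly in its link to the outcome, and much less in whether the arms happen to differ on it. The protocol names ulcer size as a driver of healing and measures it on everyone, but would use it only if the arms are judged unequal. Two things follow.

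1. **Precision.** When no imbalance is declared, the variation in healing that area explains stays unexplained. In a survival model that costs power.
2. **Choice.** The covariates of the multilevel estimate are settled after the baseline comparison has been seen, by a judgement of relevance that has no stated limit.

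Only five clinics per arm are allocated, so chance differences in case-mix between arms can be appreciable and yet fall short of anyone's idea of relevant.

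**Working it through.** **1. Inputs from the protocol article.** Three-month healing of 44%, a difference of 15% (read as percentage points), 125 patients and 5 clinics per arm, 25 per clinic, intra-cluster correlation 0.05 (Sample size); one year of follow-up (Interventions); 40–70% three-month healing by ulcer size (Background). The protocol gives no figure for the effect of any covariate on healing, so there is no planned value to reproduce.

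**2. Target effect.** Under proportional hazards, 44% against 59% gives HR = ln(1 − 0.59)/ln(1 − 0.44) = 1.54, a log HR of 0.43.

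**3. How strong could ulcer size be?** Take the two ends of the 40–70% range as large and small ulcers (an assumption). The log-hazard contrast is ln[ln(0.30)/ln(0.60)] = ln(1.204/0.511) = 0.86. Per SD of size this is:
- 0.86/4 = 0.21 if the range spans 4 SD
- 0.86/2 = 0.43 if it spans 2 SD
- 0.86/1.60 = 0.54 if it contrasts the two halves of a normal distribution

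A plausible strength is therefore about 0.2 to 0.5 per SD.

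**4. Simulation.** Two arms of 5 × 25, exponential times, 52 weeks of follow-up, conditional HR 1.54, 600 trials per setting. Two standardized prognostic covariates have assumed strength 0.2, 0.4 or 0.6 each. The triggered rule adjusts for a covariate only if the observed difference exceeds 0.25 SD (an assumption, as the protocol gives no threshold).

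No clinic effect:

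| Strength | Unadjusted HR, power | Triggered HR, power | Always adjusted HR, power |
|---|---|---|---|
| 0.2 | 1.51, 87% | 1.51, 87% | 1.55, 89% |
| 0.4 | 1.44, 78% | 1.45, 79% | 1.55, 90% |
| 0.6 | 1.37, 64% | 1.38, 67% | 1.56, 90% |

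The gain from always adjusting is about 2, 12 and 26 points.

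With a clinic effect (assumed SD 0.3 on the log hazard, and a clinic component of 0.22 SD in the covariates), Cox models that ignore clinic rejected a true null in 16–27% of runs. Power was therefore taken from the empirical spread, as Φ(mean log HR/SD − 1.96):

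| Strength | Unadjusted | Triggered | Always adjusted |
|---|---|---|---|
| 0.2 | Φ(0.376/0.217 − 1.96) = 41% | Φ(0.383/0.219 − 1.96) = 42% | Φ(0.401/0.229 − 1.96) = 42% |
| 0.4 | Φ(0.351/0.220 − 1.96) = 36% | Φ(0.365/0.214 − 1.96) = 40% | Φ(0.416/0.231 − 1.96) = 44% |
| 0.6 | Φ(0.307/0.211 − 1.96) = 31% | Φ(0.317/0.201 − 1.96) = 35% | Φ(0.418/0.239 − 1.96) = 42% |

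The gain is about 1, 8 and 11 points. Monte Carlo error is about 1–2 points, so the smallest gain is not distinguishable from none.

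**5. From two covariates to one.** Two independent covariates of strength g act like one of strength √2·g, that is 0.28, 0.57 and 0.85. Ulcer area alone, at the 0.2 to 0.5 of step 3, therefore lies below the middle row: less than about 8 points with a clinic effect and less than about 12 without. The top rows need a second strong covariate.

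**6. Under no treatment effect.** The average HR stayed between 0.99 and 1.02 in every analysis. Without a clinic effect, rejection was 3–5% whether adjusted or not.

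**The case against.** **The unadjusted estimate is legitimate.** This stands. A reader might infer from the smaller unadjusted HR that the plan yields a biased result. It does not. The gap between 1.54 and 1.37–1.51 is non-collapsibility: the unadjusted HR describes a marginal effect and the adjusted one a conditional effect. In a trial that calls its context pragmatic, the marginal effect is a defensible target.

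**The main result cannot be selected.** This also stands. The log-rank and Cox results are fixed in advance and reported whatever the balance. The analysts are blinded to group, and the trigger looks at baseline data, not outcomes. The freedom of choice touches only the multilevel estimate, where it remains because no threshold is given.

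**The loss from the actual rule is unknown.** Largely right. At 0.25 SD with no clinic component, the rule fires for one covariate in about 5% of comparisons (standard error √(2/125) = 0.126 SD), so it can recover little. With an intra-cluster correlation of 0.05 for the covariate (design effect 2.2), the standard error is √(2 × 2.2/125) = 0.188 SD, and a 0.1 SD threshold would fire in about 59%. In the clinic-effect simulation the triggered rule recovered about half the gain at strength 0.4 and less at 0.6.

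**Duration is not supported.** Correct. The Background links healing to size, not to duration. Also, only the main ulcer is measured while the outcome is healing of all ulcers, so the strength of area for this outcome is itself uncertain.

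**An article leaves covariates to the analysis plan.** This does not remove the point. The article does not stay silent; it sets a rule that depends on the data, and a fixed covariate list would replace that rule.

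**Conclusion.** The point holds as an improvement in efficiency and in prespecification. The plan is not invalid on this ground: omitting ulcer area produces neither bias under the null nor false positives. What the rule costs is precision, along with a fixed definition of the adjusted estimate.

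The documents do not determine how much precision. Under two covariates of assumed strength 0.2–0.6 per SD each, always adjusting gains about 1 to 11 points of power with clinic variation and about 2 to 26 without. For area alone, at the strength suggested by the protocol's own 40–70% range, the gain should lie in the lower part of those ranges. These figures compare always adjusting with never adjusting; the shortfall of the imbalance rule itself depends on a threshold that is not stated.

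A reader might also infer that the trial's power is so low that this loss is decisive. Whether the planned size delivers its stated 80% is a separate question about the sample-size calculation, and this point does not rest on it.

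**What to change.** In the Data analysis section, replace the sentence on unbalanced variables. State that the primary clinic-adjusted survival model always includes log baseline area of the main ulcer, whatever the observed balance, and that the model without it is reported as a sensitivity analysis. Drop selection by imbalance; the baseline comparison can remain as description.

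Ulcer duration, also recorded at T0, may be named in advance if the investigators consider it prognostic, but the protocol itself gives no ground for requiring it.

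The cost is one or two sentences. Area is already measured on every patient at T0, so there are no new data, no extra visits and no change to the number of patients. The wording should be fixed before any comparison of the arms is seen.
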